#### Clinical Outcomes

Measures for fitness (primary), self-report (secondary), and anthropometric and physical outcomes (exploratory outcomes) are repeated at baseline, T1 (immediately after exercise program, month 3), and T2 (6 months after exercise program, month 9).

##### Primary Clinical Outcome

Cardiorespiratory fitness will be assessed by a graded exercise test using the modified Bruce protocol [143]. Directly measured peak volume of oxygen (mL/kg/minute) and anaerobic threshold will be obtained using a metabolic cart (TrueOne 2400, Parvo Medics) with continuous gas exchange analysis during incremental treadmill walking to volitional peak capacity. Blood pressure and arterial oxygen saturations are measured at rest and during exercise. Absolute and relative test termination criteria are based on standardized guidelines[144].

##### Secondary Clinical Outcomes

We will gather preliminary data on a number of exploratory variables which have been identified as important to understanding the potential impact of the intervention on patient-relevant and clinically-relevant outcomes. They are being collected to examine whether they are feasible to collect in a larger trial and whether they are responsive (sensitive to change) to the intervention [145,146].

###### Patient-Reported Clinical Outcomes

Godin-Shepherd Leisure-Time Exercise Questionnaire: a brief validated 3-item questionnaire that asks respondents to report on typical weekly exercise habits [147]Functional Assessment of Cancer Therapy—Breast: generic quality of life measured with 44 self-report items [148]Spielberger's State-Trait Anxiety Inventory—State [149]: a widely used 20-item measure of state anxietyCenter for Epidemiological Studies—Depression Scale short form: a 10-item self-report measure of depressionFunctional Assessment of Cancer Therapy—Fatigue subscale [150]: a 13-item measure of fatigue in cancer patientsBreast Cancer Prevention Trial Symptoms Scale: a 42-item scale to assess side effects associated with the treatment of breast cancerFear of Recurrence Questionnaire: assesses anxiety about breast cancer recurrence [151]Physical Activity Group Environment Questionnaire [152]: assesses group cohesion during exerciseBrief Pain Inventory [153]: a widely used measure to rapidly assess the severity of pain and its impact on functioningMultiple Intervention Satisfaction Survey: an investigator-generated instrument that facilitates intervention participants in rank-ordering discrete intervention components with respect to how helpful they are in achieving outcomes during study participation. Additional items facilitate participant suggestions for deleting intervention components deemed (by participants) as of negligible benefit.

###### Anthropometric Clinical Outcomes

Body composition is assessed via body mass index, waist circumference, and body fat percentageWaist circumference is measured according to the World Health Organization protocol (midpoint between lowest rib and iliac crest)Body fat percentage is measured using bioelectrical impedance analysis [144]Grip strength is measured using a Jamar dynamometer according to the Canadian Society for Exercise Physiology 2004 protocol

## Results

### Primary-Secondary Outcome Assessment

Recruitment and retention rates will be assessed [154] with estimates for participants with complete data per outcome and time point divided by the total number of study participants. Interpretation of the interview output (acceptability) will be based on inductive and deductive analyses and use of the constant comparative method [155].

Variability of the main and interaction effects will be examined in the primary clinical outcome (cardiovascular fitness) and each secondary outcome using separate repeated measures analysis of covariance models with Bonferroni corrections applied to the models. Hedges’ *g* and associated confidence intervals [156] will be calculated as an estimate of the effect size both over time (within groups) and between groups [157]. Missing data will be evaluated on a case-by-case basis such that drop-outs will be excluded. Intention-to-treat (all consented subjects) analysis will employ a last observation carried forward approach to evaluate all data collected. Per protocol analysis will evaluate data on subjects who participated in 50% of group exercise sessions (comparing intervention with control subjects), while experimental subjects will have the additional criteria of participating in 50% of health coaching calls.

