### Recruitment and Randomization

After identification from weekly generated clinic lists and chart reviews, patients will be approached by a member of their clinical team, and interested patients will meet with a research assistant for additional study explanation and eligibility screening. Participants will also be recruited by advertisement flyers located in hospital common areas. Eligibility will be ascertained in person when possible, with written consent obtained in person prior to randomization. After participants complete baseline questionnaires and initial physiological assessments, stratification-related data (age, AHT status) will be emailed to a biostatistician in the Department of Biostatistics at PMCC who will perform randomization and then send a study identification with intervention or control group allocation.

Inclusion and exclusion criteria for study.Inclusion criteria:Less than 2 years of completion of adjuvant therapy with the exception of hormone therapy for stage 0 to IIIASelf-report of fewer than 60 minutes of weekly preplanned physical activityPhysician clearance for moderate-to-vigorous physical activityEnglish proficiencyAbility to attend exercise training sessions and study assessments at prescribed intervals for 9 monthsExclusion criteria:Plans to join a weight loss or exercise program within 9 monthsCurrent pregnancy or planned pregnancy within 9 monthsPlanned surgery during study durationUnwillingness to be randomized

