### Sample Size and Power

We previously conducted a simulation for a range of sample sizes and different SD values for precision of the treatment effect estimate. The precision of the estimate is represented by the inverse of the margin of error. Type I error was set at α=0.05 and power at 80%. From our simulation result, a sample size of 35 to 40 was at the elbow point of the curves, indicating the precision of estimates did not proportionally increase with a larger sample size. Therefore, our projected sample size is 80 participants (40 per arm) [158]. With an anticipated drop-out rate of up to 25% [73], we will recruit 107 participants and examine the variance in primary outcomes with precision (low standard error >0.1), while enabling further calculations of effect sizes for planning the phase 3 trial [154]. The large majority of women return to PMCC for follow-up appointments typically scheduled every 3 to 6 months. Based on data from the PMCC registry, eligibility criteria, and expected participation rates, we anticipate recruiting 8 to 10 participants per month. Study duration is estimated at 30 months.

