### Interpretation of Results

Interpretation of the effect size and mean difference scores and calculation of the sample size for a larger RCT (fitness outcome) will be based on a minimally important clinical difference (MCD) of 3.5 mL/kg/minute (peak volume of oxygen) between the 2 experimental groups at the 6-month T2 assessment [159,160]. We regard the MCD as a small effect size [159]. With pilot results, we will better estimate small, medium, and large effect sizes for the planned (full-scale) RCT.

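### The plan does not say which missing-data rule governs which analysis, and last observation carried forward can bias the month-9 fitness comparison

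*Protocol article*

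**What the plan says.** All the rules stand together in Primary-Secondary Outcome Assessment. The models are "separate repeated measures analysis of covariance models with Bonferroni corrections applied to the models". Then come three consecutive statements:

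- The first deals with women who leave: "Missing data will be evaluated on a case-by-case basis such that drop-outs will be excluded".
- The second, which follows directly, sets the widest analysis: "Intention-to-treat (all consented subjects) analysis will employ a last observation carried forward approach to evaluate all data collected".
- The third sets the narrowest analysis, by attendance: "Per protocol analysis will evaluate data on subjects who participated in 50% of group exercise sessions". The intervention arm has an added requirement on coaching calls.

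Other sections bear on these rules:

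- Recruitment and Randomization has "written consent obtained in person prior to randomization". Allocation follows only after the baseline questionnaires and physiological tests.
- Clinical Outcomes gives two visits after baseline: "T1 (immediately after exercise program, month 3), and T2 (6 months after exercise program, month 9".
- Sample Size and Power has "With an anticipated drop-out rate of up to 25" percent and a target of 107.
- Interpretation of Results reads the fitness result against this yardstick: "minimally important clinical difference (MCD) of 3.5 mL/kg/minute (peak volume of oxygen) between the 2 experimental groups at the 6-month T2 assessment".
- The Introduction (Background) states that the benefits of activity last only while the exercise continues.

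**The concern.** **Unassigned rules.** One sentence removes drop-outs and the next keeps everyone. Neither is tied to a named analysis, and no analysis is called primary. The first sentence also joins case-by-case judgment to a blanket exclusion. The exclusion cannot simply be the per-protocol rule, because that set is defined separately by attendance. If this stays open until the data are seen, the choice can follow the results.

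**The set itself.** A woman who consents but withdraws before testing has no arm and no baseline peak VO2, so nothing can be carried forward for her.

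**The imputation.** Month 3 is the end of the supervised program and month 9 is the maintenance assessment. For women lost between the two, carrying forward assumes that fitness was fully kept, against the article's own premise about stopping exercise. For women lost before month 3 it assumes that nothing was gained. In both cases a guessed value enters the model as if it had been measured.

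What is at stake is Aim 3, the pilot estimate of efficacy on fitness, and the effect size with its interval that the Discussion wants for later planning.

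**Working it through.** **1. The plan's own figure.** 80 / (1 − 0.25) = 106.7, rounded up to 107, which reproduces the target. Up to 0.25 × 107 = 26.75, about 27 women, may drop out. The exclusion rule would then analyse about 80 women. The carry-forward rule would analyse 107, with up to 25% of month-9 values imputed.

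**2. Inputs not in the article, assumed here.** SD of peak VO2 5 mL/kg/min; correlation 0.7 between any two visits; 54 women per arm (40 / 0.75 = 53.3, rounded up); gain of 2.0 at month 3 in both arms. Unless stated otherwise, drop-outs follow the same true course as the others in their arm.

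**3. Expected month-9 gain under carry-forward.** Let d be the fraction lost in an arm, q the share of those lost after month 3, and g1 and g2 the mean gains at months 3 and 9. The arm mean becomes (1 − d) × g2 + d × q × g1.

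- *True difference 1.5 (intervention 2.0, control 0.5), 25% lost per arm, all after month 3.* Intervention 0.75 × 2.0 + 0.25 × 2.0 = 2.0. Control 0.75 × 0.5 + 0.25 × 2.0 = 0.875. Difference 1.125, which is 25% too small.
- *Same, but all lost before month 3.* Intervention 0.75 × 2.0 = 1.5. Control 0.75 × 0.5 = 0.375. Difference again 1.125.
- *No true difference (both arms 0.5), late loss of 35% in intervention and 15% in control.* Intervention 0.65 × 0.5 + 0.35 × 2.0 = 1.025. Control 0.85 × 0.5 + 0.15 × 2.0 = 0.725. False difference +0.30, favouring the arm that lost more women.
- *No true difference, 25% late loss in each arm.* Both arms 0.75 × 0.5 + 0.25 × 2.0 = 0.875. Difference 0, although each arm's maintenance is overstated by 0.375.

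**4. Precision and coverage in the first scenario.** The residual SD after baseline adjustment is 5 × √(1 − 0.7²) = 3.57. With all 54 per arm counted as observed, SE = 3.57 × √(2/54) = 0.687. With the 40.5 per arm actually observed, SE = 3.57 × √(2/40.5) = 0.79. The bias is 0.375 / 0.687 = 0.55 standard errors, so coverage is about Φ(1.41) − Φ(−2.51) = 0.921 − 0.006 = 0.915. Simulation of 3,000 trials agrees: carry-forward averages 1.12 with 91.5% coverage, and a baseline-adjusted analysis of the observed values averages 1.49 with 94.8%.

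**5. SD and Hedges' g.** In simulation the pooled month-9 SD is 5.00 under carry-forward and 4.98 in observed data, so it hardly moves. Before the small-sample correction, g falls from 1.5 / 5 = 0.30 to 1.125 / 5 = 0.225, through its numerator alone.

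**6. Sample size of the later trial.** With a difference fixed at 3.5 and SD 5 (two-sided 0.05, 80% power) it is 33 per arm, whatever difference the pilot observes. Only if the attenuated observed difference replaced it would N rise, by 1 / 0.75² = 1.78.

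**The case against.** **The rules may not conflict.** The three statements can be read as three analyses: completers, intention-to-treat, and per protocol. This is a fair reading, and it stops one from saying that the rules flatly contradict each other. But the article does not label the first set or name the primary one, so the clarification is still needed.

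**The bias is conditional and modest beside pilot noise.** This stands. It is nil with equal late loss and equal decline, and the article gives neither the timing of drop-out nor its split by arm. In the first scenario the bias of about 0.37 compares with a standard error of 0.7 to 0.8, and root mean squared error is 0.79 for carry-forward against 0.80 for observed data.

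**The comparison favours observed data by construction.** Drop-out was simulated as unrelated to outcome within each arm, and the proposed mixed model was not itself simulated. Observed data can also mislead. Suppose both arms gain 3.5 by month 3, completers keep 3.5 (intervention) or 0 (control), and the 25% lost after month 3 fall back to 0 in both arms. The true difference is 0.75 × 3.5 = 2.625. Carry-forward gives 3.5 − 0.875 = 2.625, and observed values alone give 3.5. This is why the fix includes a return-toward-baseline analysis.

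**Stronger readings that the document does not support.** A reader might infer that carrying forward assumes full maintenance in everyone who left, but that is true only of women lost after month 3. A reader might infer that the SD is distorted too, but under these assumptions it is not. A reader might infer that the full trial would be oversized by 1.78, but Interpretation of Results bases its sample size on the fixed 3.5. Sample Size and Power and the Discussion do mention effect sizes for planning, so that route is not closed, but it is not the stated rule.

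**This is a pilot, and a fuller plan may exist.** Feasibility and acceptability come first among the aims, and drop-out reasons and missing-data proportions will be recorded. That lowers the severity. The point nevertheless rests on rules that the article states, not on detail it leaves out.

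**Conclusion.** The point holds in limited form, at moderate severity. As written, the exclusion rule and the intention-to-treat rule are not assigned to analyses, no primary analysis is named, and everyone who consented is the wrong set for a randomized comparison. Carrying forward suits a maintenance endpoint poorly: it fills the month-9 value with end-of-program fitness or with baseline, and counts it as measured.

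The size depends on assumptions that the article does not supply. Under those used here, a true difference of 1.5 is estimated as about 1.12 with about 91.5% coverage. A false difference of about +0.3 arises under the null with 35% versus 15% late loss, and none arises with equal late loss and equal decline. The direction is therefore not fixed. The target of 107 and a full-trial sample size built on the 3.5 difference are unaffected.

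**What to change.** Before month-9 data are analysed:

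- Define the primary analysis set as all randomized participants, analysed as allocated, in place of all who consented.
- Delete the exclusion sentence, or label it as a supportive completers analysis.
- Replace last observation carried forward with a likelihood-based repeated-measures model for peak VO2 at months 3 and 9 that uses every observed value, or with multiple imputation. Include baseline peak VO2 and the two stratification factors (age group and adjuvant hormone therapy) as covariates.
- Add one sensitivity analysis in which women lost before month 9 return toward their baseline value.

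The cost is a change of wording, slightly more analysis work, and somewhat wider but more honest intervals. No new data or participants are needed.

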### Sample Size and Power

We previously conducted a simulation for a range of sample sizes and different SD values for precision of the treatment effect estimate. The precision of the estimate is represented by the inverse of the margin of error. Type I error was set at α=0.05 and power at 80%. From our simulation result, a sample size of 35 to 40 was at the elbow point of the curves, indicating the precision of estimates did not proportionally increase with a larger sample size. Therefore, our projected sample size is 80 participants (40 per arm) [158]. With an anticipated drop-out rate of up to 25% [73], we will recruit 107 participants and examine the variance in primary outcomes with precision (low standard error >0.1), while enabling further calculations of effect sizes for planning the phase 3 trial [154]. The large majority of women return to PMCC for follow-up appointments typically scheduled every 3 to 6 months. Based on data from the PMCC registry, eligibility criteria, and expected participation rates, we anticipate recruiting 8 to 10 participants per month. Study duration is estimated at 30 months.

### Interpretation of Results

Interpretation of the effect size and mean difference scores and calculation of the sample size for a larger RCT (fitness outcome) will be based on a minimally important clinical difference (MCD) of 3.5 mL/kg/minute (peak volume of oxygen) between the 2 experimental groups at the 6-month T2 assessment [159,160]. We regard the MCD as a small effect size [159]. With pilot results, we will better estimate small, medium, and large effect sizes for the planned (full-scale) RCT.

## Discussion

While current data suggest an important role for physical activity in disease control and the long-term health of cancer survivors, most breast cancer survivors are inactive. This discrepancy must be addressed with physical activity promotion that supports long-term exercise adherence. To date, research has focused on specific physical activity components linked to clinical benefits, but insufficient attention has been paid to factors influencing long-term physical activity maintenance. The current project employs a behavioral support intervention that assists breast cancer survivors in adopting physical activity and maintaining physical activity adherence. While multiple RCTs demonstrate effectiveness in physical activity participation during trial conduct, decreases in physical activity after trial conclusion are an important concern. It is not yet known the degree to which smartphone-enabled health coaching combined with wearable fitness technology can contribute to the lifestyle changes required for breast cancer survivors to maintain healthy physical activity over the longer term.

Our commitment to the devised intervention (combining phone-based health coaching, Fitbit step tracking, health tracking software, face-to-face exercise classes, and fitness testing) accepts the design limitation of being unable to identify which intervention components provide key contributions to significant effects; future studies may be needed to tease out what worked best in further streamlining the intervention. However, we have mitigated limitations by logging all phone counseling calls undertaken (registering time durations per call) and additionally itemizing and quantifying all use of the health tracking software, Connected Wellness (NexJ Health Inc). Furthermore, we track all Fitbit use, including use patterns per time period (day, week, and month). Additionally, use of the Multiple Intervention Satisfaction Survey facilitates each participant in subjectively ranking the intervention components on importance and suggesting deletions of components that have not been significantly helpful. These efforts will enable us to learn about the prioritization of intervention components from each subject’s perspective. Another limitation entails not knowing which allocations of staff time (to the intervention) represent a cost savings when compared to other physical activity promotion approaches. Therefore, we will carefully assess staff time, preparing for ascertaining this cost dimension in the future.

This pilot will document the implementation of the methods and intervention, preliminary outcomes, and acceptability of the interventions by qualitative interview. It will assess effect size in primary and multiple secondary outcomes with corresponding confidence intervals for more definitive sample size calculations. Although pilot results will provide a foundation for full-scale RCT planning, we anticipate challenges for which we currently have only partial or potential solutions. For example, we will only have suggestive data for assessing specific intervention components and for selecting the optimal subset for full RCT testing. Furthermore, as a pilot study, we are still refining the ultimate sample size of the planned full-scale RCT. Additionally, while control subjects receive an approximation of current standard care for exercise promotion (at ELLICSR), we cannot fully account for the attentional differences in intervention and control conditions. Nonetheless, this pilot is a distinct step forward in addressing a gap in the promotion of longer term exercise adherence for breast cancer survivors.

## Abbreviations

ACSM: American College of Sports Medicine
AHT: adjuvant hormone therapy
CBT: cognitive behavioral therapy
CEP: certified exercise physiologist
ELLICSR: Electronic Living Laboratory for Interdisciplinary Cancer Survivorship Research
MCD: minimally important clinical difference
MI: motivational interviewing
MVPA: moderate-to-vigorous physical activity
PMCC: Princess Margaret Cancer Centre
RCT: randomized controlled trial
RKin: registered kinesiologist
